### Study population

#### Inclusion criteria

Participants are required to be between 18 and 75 years old and diagnosed with: stage IV solid cancer specifically colon, breast or non-small-cell lung cancer, have an Eastern Cooperative Oncology Group ECOG Performance Status of ≤1, and be on standard first-line chemotherapy; malignant blood cancer and have received an autologous transplant or non-localised lymphoma and be on immune therapy; schizophrenia including first-episode psychosis or other psychotic disorders; or clinically stable (no exacerbation, antibiotic treatment, systemic corticosteroid therapy or hospitalization in the previous 30 days) COPD with a BODE index of 3–7 and a life expectancy > 2 years. In addition, the following are required for patients to be eligible for inclusion: good renal, liver and blood function, with haemoglobin levels > 10 g/dl, a platelet count > 50,000, neutrophil count > 1000, and Karnofsky Performance Status score > 60, and an Eastern Cooperative Oncology Group Performance Status score ≥ 1.

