### Randomisation

Once informed consent has been obtained and baseline measurements have been taken, patients will be randomised blindly and centrally to either the EG or PVS group, stratified by illness type, at the coordinating centre, the Primary care Research Unit of Bizkaia of the Biocruces Bizkaia Health Research Institute. The randomization will be performed using computer-generated random numbers in a 1:1 ratio, stratified by illness type, with a block size of 4 or 6. (Fig. 1).

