Physical activity performed. For this, each participant will be fitted with an Actigraph wGT3X-BT accelerometer on their right hip at the level of the iliac crest and an HR monitor band (Polar OH1). They should wear these monitors for a week and complete a daily record of their activity, to monitor activity counts during different intensities of activity. To analyse these data, we will assess the activity counts, which correlated with LT1 during the incremental test, and thereby be able to assess their weekly physical activity based on personal activity count thresholds.Body composition (OMROM body fat percentage), body mass index and abdominal circumference, estimated cardiovascular risk and the onset of any cardiovascular eventsPsychological changes assessed using Goldberg’s 12-item General Health Questionnaire (GHQ-12) and the Duke Social Support IndexIn addition, in the case of schizophrenia, changes in mental state assessed using the Positive and Negative Syndrome Scale (PANSS), and the severity of the patient’s condition and changes therein during the course of the programme assessed using the Clinical Global Impression (CGI) and the Global Assessment of Functioning (GAF) scaleLipid profile, as well as levels of C-reactive protein, glucose, insulin and specific exercise-related parameters: adiponectin, BDNF in participants with schizophrenia, TNF-α in those with cancer and Il-1 and Il-6 in those who have COPD or are transplant recipients (at baseline and 3 months).Potential predictive, modifying and confounding factors: sex, age, comorbidities (Adjusted Clinical Groups Case-Mix System), risk factors, socioeconomic status, drug treatments and characteristics of each chronic condition.

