### Statistical analysis

The statistical analysis will be performed on an intention-to-treat basis, comparing changes observed from baseline throughout the year of follow-up in participants assigned the EG and PVS group, adjusting for baseline, using mixed-effect analysis of covariance (linear for continuous outcomes and logistic for dichotomous outcomes). The effect of time on the repeated measures in each participant will be estimated and the hypothesis of significantly different (*p* < 0.05) changes in the EG and PVS group will be tested, assessing a treatment group-time interaction term. These models will include an additional effect characteristic of each group and the interaction between the conditions and the effect of the intervention (GE/PVS). The comparisons will be adjusted for potential confounders. The aforementioned effects will be considered fixed and patients and primary care centres will be included as random effects in the intercept, time slope and effect of the programme. Models will be simplified with backward and forward selection using Likelihood ratio tests (selection criteria, *p* < 0.05). A sensitivity analysis will be performed including/excluding outliers. Based on these models, the effect attributable to the intervention will be estimated, calculating the mean differences between groups estimated at each of the follow-up points (adjusted odds ratios for dichotomous outcome variables) and 95% confidence intervals. Before such analysis, potential interaction effects between the specific illness group of the participant and the effect of the interaction would have been ruled out. Regarding missing values, these longitudinal mixed effect models are one of the best approaches for managing missing data. Analysis will be performed by pre-established groups to test hypotheses that the programme is more effective in patients with mental illness, young people, males, those with a high socioeconomic status, less advanced stages of illness and those with certain comorbidities, evaluating an interaction term between these covariates and the intervention (*p* < 0.005). An analysis will also be carried out by protocol, considering the actual dose of physical activity to which each participant has been exposed. Finally, the cost-effectiveness and incremental cost-utility ratios and their confidence intervals will be estimated using resampling techniques (bootstrapping) and a sensitivity analysis will be performed, changing the assumptions of the analysis. The statistical analysis will be performed with SAS and R packages. No imputation method will be used to handle missing data since longitudinal mixed models based on maximum likelihood estimation are more appropriate to deal with missing data [42] than common imputation methods such as last observation carried forward, complete case analysis or other possible forms of imputation.

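### The blanket no-imputation rule rests on a reason that covers missing follow-up outcomes only, so a randomised patient missing an included baseline covariate drops out of the adjusted analysis

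*Protocol article*

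**What the plan says.** All of the following is in the protocol article.

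- **The rule.** Statistical analysis: "No imputation method will be used to handle missing data since longitudinal mixed models based on maximum likelihood estimation are more appropriate". The sentence goes on to rank mixed models above alternatives: "than common imputation methods such as last observation carried forward, complete case analysis or other possible forms of imputation". The rule is not limited to follow-up outcomes, and no other reason is given.
- **The covariates.** The models are fitted "adjusting for baseline, using mixed-effect analysis of covariance (linear for continuous outcomes and logistic for dichotomous outcomes"). In addition, "The comparisons will be adjusted for potential confounders". Outcome measures lists the candidates: "Potential predictive, modifying and confounding factors: sex, age, comorbidities (Adjusted Clinical Groups Case-Mix System), risk factors, socioeconomic status, drug treatments", together with characteristics of each illness.
- **Model building.** Statistical analysis simplifies the models by backward and forward selection with likelihood ratio tests at p < 0.05. It also tests interactions of the intervention with covariates such as socioeconomic status, illness stage and comorbidity.
- **Timing.** Randomisation: "Once informed consent has been obtained and baseline measurements have been taken, patients will be randomised blindly and centrally". This puts baseline measurement before allocation. It does not make completeness of every covariate a condition of randomisation.
- **Analysis population.** Statistical analysis declares an intention-to-treat basis.

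**The concern.** A longitudinal mixed model fitted by maximum likelihood has a distribution for the outcomes. A patient with some follow-up visits missing still contributes the visits that were observed, and the estimate is valid if the outcomes are missing at random. The model has no distribution for its covariates. If an included covariate is missing, standard software removes all of that patient's rows.

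So the reason given does not support the rule as worded. Wherever an included covariate is incomplete, randomised patients with observed outcomes leave the comparison, and the rule forbids the usual remedy. Socioeconomic status, comorbidities and drug treatments are typical candidates. At stake are the number of patients analysed, the precision of the adjusted estimates, and consistency with two statements the section makes itself: the intention-to-treat basis and the rejection of complete case analysis. Forward and backward selection adds a smaller risk, because the set of patients can change as an incomplete covariate enters or leaves.

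**Working it through.** **1. The plan's own power figure.** Sample size gives 370 patients, 30% loss, SD 40 s, intra-patient correlation 0.6, and differences of 6, 12 and 24 s at 3, 6 and 12 months (2 s per month), with power over 90%. I assume a two-sided 5% test, compound symmetry, visits at 0, 3, 6 and 12 months, and completers only: 370 × 0.7 = 259, or 129.5 per arm.

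- Spread of visit times about their mean of 5.25: 27.56 + 5.06 + 0.56 + 45.56 = 78.75 (unrounded terms).
- Residual variance: 40² × (1 − 0.6) = 640.
- SE of the difference in slopes, with a separate intercept per arm: √(2 × 640 / (129.5 × 78.75)) = 0.354 s per month.
- Power = Φ(2/0.354 − 1.96) > 99.9%. With a baseline mean common to both arms it is also above 99.9%.

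The stated figure is therefore reproduced for the trend test.

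**2. How many patients a missing covariate removes.** The documents give no rate, so this is an illustration. With k covariates each missing independently in a proportion p, the share dropped is 1 − (1 − p)^k, and the standard error is multiplied by 1/√(1 − share).

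| k = 6 | Share dropped | Left of 370 | Left of 259 | SE factor |
|---|---|---|---|---|
| p = 2% | 1 − 0.98⁶ = 11.4% | 328 | 229 | 1.06 |
| p = 5% | 1 − 0.95⁶ = 26.5% | 272 | 190 | 1.17 |

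**3. What that does to power.**

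- *Walk-time trend.* With 30% of patients deleted, 90.65 completers per arm remain. The SE is √(1280 / (90.65 × 78.75)) = 0.423, and power is Φ(2/0.423 − 1.96) = 99.7%. With a common baseline mean it stays above 99.9%.
- *Single visit.* For the 12 s difference at 6 months, analysis of covariance has SD 40 × √(1 − 0.36) = 32. Power is 85.5% with no deletion, 81.7% with 10% deleted and 77.0% with 20% deleted.
- *Quality of life.* The stated 90% cannot be reproduced, because no SD is given for the SF-36. Taken at face value and scaled as Φ((1.96 + 1.2816) × √(1 − share) − 1.96), it becomes 86% to 79% under the assumptions in step 2.

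**4. Whether deletion distorts the estimate.** A simulation used 370 patients, cumulative dropout of 10%, 20% and 30%, a true 12-month difference of −24 s, and one covariate missing in an assumed 15%.

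- The adjusted model kept about 283 patients, against 333 when the covariate was left out.
- Patients with partial follow-up were still used. In one simulated trial, 58 of the 270 retained patients had only one or two of the three follow-up visits.
- Over 150 runs the mean estimate was −24.9 both with and without deletion. The shared gap of 0.9 is about three Monte Carlo standard errors (3.6/√150 = 0.29), so I repeated the design with 4,000 runs, weighting by the known covariance. The means were then −24.0 with and without deletion. This held when missingness was completely at random and when it depended on the baseline outcome.
- In the 4,000 runs the SD of the estimate rose from about 3.9 to 4.2, close to the √(333/283) = 1.08 expected from patient numbers alone.

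**5. Likelihood ratio tests.** The statistic compares two models on the same data. If a candidate covariate is missing for some patients and each model uses every patient it can, the two likelihoods come from different patients and their difference has no chi-square reference. Fixing one set in advance removes the problem. The plan does not say which will be done.

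**The case against.** **The sentence is really about outcomes.** The comparators it names belong mostly to missed visits, and handling of missing covariates is commonly left to an analysis plan. This is a fair reading of intent, and it is why the point is modest. But the rule is stated and closed, not left open: an analysis plan that filled in covariates would contradict the protocol as worded.

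**Most covariates should be complete.** Age, sex, illness type and the pre-randomisation baseline outcome should rarely be missing. This stands. A reader might infer that every adjusted comparison loses patients; only those that include an incomplete covariate do.

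**It does not become a complete-case analysis.** This stands for outcomes, as step 4 of the working shows. The deletion is on covariates only.

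**Illness-specific characteristics.** Outcome measures includes "risk factors, socioeconomic status, drug treatments and characteristics of each chronic condition", and Inclusion criteria uses "COPD with a BODE index of 3–7" for one illness only. A reader might infer that adjusting for such an item would shrink the pooled model to one stratum. The documents do not support that. A value that does not apply is not a missing value, coding it within its illness is not imputation, and nothing says it would enter as a bare term.

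**Harm is not shown to include bias.** This stands. Covariates fixed before allocation should lead to similar deletion in both arms, and the simulation found no shift.

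**Invalid likelihood ratio tests are conjecture.** This stands in part. The tests are at risk only if the patient set is allowed to vary.

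**Conclusion.** The point holds in a limited form. The reason offered for ruling out imputation covers missing follow-up outcomes, while the rule covers everything. Where an included baseline covariate is missing, the adjusted model loses a randomised patient whose outcomes were observed, contrary to the intention-to-treat basis and to the rejection of complete case analysis.

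The cost is patients and precision: 11% to 26% of patients and standard errors 6% to 17% larger, if six covariates are each 2% to 5% missing independently. The number of covariates, the rates and the independence are all assumptions, and the real loss could be smaller.

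Bias in the treatment comparison was not demonstrated. A reader might also infer that the trial's power is in danger. For the walk-time trend it is not, even with 30% of patients deleted. The loss would be felt in single-visit estimates and possibly in quality of life, where the stated power cannot be checked. The change is worth making because it costs almost nothing.

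**What to change.** Replace the blanket sentence with one paragraph in Statistical analysis that does five things:

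1. Limits the no-imputation rule to follow-up outcomes, which the likelihood-based mixed model handles under missing at random.
2. For the adjusted main comparison, fills missing baseline covariates without regard to allocation, so that all randomised patients with outcome data stay in. Use the illness-stratum mean for continuous items and a separate category for missing in categorical items. This is sound in a randomised comparison because baseline values cannot depend on the arm.
3. Codes any illness-specific characteristic within its illness, for example centred there and set to 0 in the other illnesses.
4. Fits all nested models in the selection procedure to one fixed set of patients.
5. Treats missing moderators in the interaction tests separately, since simple filling is suited to adjustment and not to estimating effect modification.

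The cost is a paragraph of wording and trivial programming. No new data are needed, and the outcome model is unchanged.

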
### Quality control

Various processes have been undertaken seeking to guarantee the quality of the study data, and thereby maximise the validity and reliability of the measurement of outcomes and study findings. These are:
Preparation of documents for the study process including fieldwork manuals, material for training concerning intervention measurements, educational leaflets and lists of measurements for exercise and health professionalsWritten documentation: electronic and hard copies of the protocol, signed consent forms, and patient results stored under lock and keyTraining for those in charge of the standardisation of the study processTraining for exercise and health professionals concerning the study characteristics and procedures, and, in particular, the quality of life interview to be carried out with the patientsHolding of regular meetings: with the coordinator of the study and with the principal investigator for auditing trial conduct (weekly)Quarterly meetings and daily contact by email with the members of the EfiKroniK group and all the participating centresProduction of monthly progress reports.

### Limitations

The structure of the study makes it impossible to blind the participants or the interveners; however, blind outcome assessors will be used. The monitoring of this intervention and data collection is complex, and therefore, data will be collected using several appropriate quality control processes, and efforts will be made to ensure standardization of the intervention. In addition, to avoid contamination of the control group, interveners will be trained, and a pilot study will also be carried out.

### Ethical and legal aspects

This study protocol complies with the Declaration of Helsinki and its revisions, as well as with good clinical practice. The Ethics Committee of the Basque Country approved the study in the health centres, and the conduct of the study will be monitored to ensure it implemented in compliance with the established regulations. Regarding data confidentiality, only the study researchers have access to the data of individuals who agree to participate in the study, in compliance with the Organic Act 15/1999 of December 13, on the protection of personal data and its 2011 revision.

## Discussion

This study seeks to make a substantial contribution to our knowledge concerning the effectiveness of an exercise programme that is supervised and tailored for patients with chronic illnesses run in primary care under conditions of routine clinical practice. It will investigate the minimal therapeutic dose with which the exercise stimulus received by a patient is sufficient to generate an observable improvement in his/her state of health, as well as the effect of tailoring the dose, which will enable us to identify which patients would benefit most from the prescription of exercise. Additionally, it will explore the common effect of exercise across people with a diverse group of chronic illnesses, independent of any additional effects on each of the conditions, this design being more innovative than the undertaking of separate trials for each illness.

Physical exercise interventions in healthcare settings for the treatment of chronic illnesses are still scarce [18]. EfiKroniK is a physical exercise programme carried out in a real healthcare setting in primary care exercise laboratories supervised by professionals trained in the optimisation of results obtained from exercise in terms of its therapeutic effects and impact on patient quality of life. Moreover, the exercise prescription is tailored to the status of patients at the time. This experience will provide an example of a study run from primary care that is well coordinated with hospital oncology, haematology and pulmonology departments and the local mental health network.

Physical exercise has been shown to act as a medicine in numerous chronic diseases, with a beneficial effect on their pathogenesis and symptoms [10]. Nonetheless, we still do not know the minimum dose necessary to obtain such benefits. The EfiKroniK programme will study the minimum therapeutic dose through the prescription of individualized physical exercise based on the metabolic response of each patient to a specific stimulus and the stage of their illness. We will also take into account the current recommendations to combine moderate-intensity aerobic exercises with muscle strength training [35].

Adherence to an active lifestyle is particularly important in patients with chronic illnesses as, given the characteristics of their condition, they tend to be more sedentary [43–45]. In EfiKroniK, we seek to confirm whether participating in an intervention of this sort would help to change physical activity habits and thereby increase the long-term benefits. Further, based on these data and those concerning adherence to the programme, we will perform cost-effectiveness and cost-utility analysis to confirm the feasibility of a programme such as this in healthcare services.

At the same time, the knowledge gained through the qualitative evaluation will be key the designing of a tailored implementation strategy to overcome the organizational and professional barriers that may hinder the adoption of the EfiKroniK programme under routine conditions which will be assessed in future implementation trials [44, 45]. All these data are necessary to make it possible to prescribe physical exercise in a similar way to a drug [33].

## Data Availability

Data sharing is not applicable to this article as no datasets were generated or analysed for preparation of the study protocol.

## Abbreviations

BDNF: Brain-derived neurotrophic factor
COPD: Chronic obstructive pulmonary disease
EG: EfiKroniK group
HR: Heart rate
HRR: Heart rate reserve
LT1: The first lactate threshold
MET: Metabolic equivalent
MLSS: Maximal lactate steady state
PVS: from the Spanish “*Prescribe Vida Saludable*”
VO2max: Maximum rate of oxygen consumption
